**4) Administration method**

The patients will be randomly divided into 2 groups: active drug (ghrelin (2 μg/kg) dissolved in 10 mL of saline) and placebo (10 mL of saline alone) treatment groups. The number of patients will be 30 in each group. The test drug will be intravenously administered taking 30 minutes twice a day (before breakfast and supper) for 3 weeks, and the effect will be investigated after completion of the administration.

**5) Other treatments**

Therapies (medication and oxygen therapy at home) other than treatment with the allocated drug will not be changed, as a rule. When an investigator judges that change or additional drug administration and treatment are necessary, the investigator will report it to the Study Director.

**6) Preparation of ghrelin and placebo vials and safety test**

The test drugs will be sealed into vials through an automatic aseptic operation at the pharmacy department. The safety test of injection was entrusted to Japan Food Research Laboratories ([name]). Vials randomly selected from the prepared ones were subjected to endotoxin and pyrogen tests.

**7)** **Efficacy Assessments**

Efficacy assessments are to be performed before the administration; Weeks 1, 2 and 3 after start of the administration**;** and Week 7 after start of the administration, i.e., 4 weeks after the completion of the administration with double-blind fashion.

****Before the administration and Week 3 after start of the administration****

1. Subjective symptom: QOL score (SF-36, SGRQ), MRC dyspnea scale
2. Examination: Blood pressure, Heart rate, Auscultation

(c) Body height, Body weight, BMI

(d) Blood test (blood will be collected after resting for 15 minutes)

(e) Peripheral blood examination (including differential leukocyte count)

(f) Biochemical examination (Na, K, Cl, Ca, Mg, GOT, GPT, ALP, LDH, γ-GTP, TP, ALB, T-Bil, D-Bil, T-CHO, H-CHO, TG, Cre, BUN, UA, CK, FBS, HBA1c)

High-sensitive CRP

Hormone (insulin, GH, IGF-1, DHEAS, BNP)

Visceral protein (Prealbumin, Retinol binding protein, Transferrin)

Cytokine (TNF-α, IL-6)

 Peripheral blood test, biochemistry, and DHEAS and visceral protein measurement will be performed at each institution.

 Other samples, i.e., hormones (insulin, GH, IGF-1, and BNP) excluding DHEAS, cytokines (TNF-α and IL-6), and high-sensitivity CRP will be collected to the center and collectively measured.

1. Sympathetic nerve activity (Blood / urinary adrenaline, noradrenalin)

(Plasma and acidic accumulated urine will be used for measurement in blood and urine samples.)

 Samples for sympathetic nerve activity measurement will be collected to the center and collectively measured.

(h) Arterial blood gas analysis (measured in recumbency)

(i) Pulmonary function test (flow volume and spirometric evaluation)

(j) Food intake

Food intake for 3 consecutive days was assessed before ghrelin administration and during the last week of ghrelin therapy. The food intake was averaged for 3 days. Food ingestion will start from 2,000 kcal/day and be increased when the patient eat all.

(k) 6-min Walk Test (walking distance, SpO2, heart rate)

(l) DEXA (Dual-Energy X-ray Absorbitometry); measurement of lean body mass, body mineral content, and fat mass

(m) Electrocardiogram continuously for 24 hours (Holter ECG)

(n) Cardiopulmonary exercise testing (CPET)

Analyzing expired gas, symptom-limited CPET were conducted on an electrically braked cycle ergometer. Peak oxygen uptake and workload were measured. Exercise load will be pedaling for 1 minute at 0 W followed by 5 W/min ramp.

Measurement parameters:  VO2 (VO2max), VCO2, VE (VEmax), VEmax/MVV, VE/VO2, VE/VCO2, HR, BP, O2pulse (VO2/HR), Work rate (WRmax), Borg scale, SpO2

(o) Grip strength

Peripheral muscle strength was measured by the maximal voluntary handgrip maneuver. The patients performed four maneuvers on each side with at least a 1-min interval between each of the maneuvers. The average of the best values on the left and right sides was reported.

(p) Respiratory Muscle Strength(Maximal inspiratory pressure statics maximal expiratory pressure statics): Respiratory muscle strength was examined during maximal voluntary efforts against occluded airways (Vitaropov KH-101; Chest Scientific Instruments Ltd; Westerham, United Kingdom). The patients performed four maneuvers, and the highest value was reported.

****The first day of the administration and Week 3 after start of the administration****

On these 2 days, blood will be collected before administration and 30, 60, and 120 minutes after administration to evaluate the time-course blood ghrelin and GH levels.

****Week 1 and 2 after start of the administration****

1. Examination: Blood pressure, Heart rate, Auscultation
2. Body height, Body weight, BMI
3. Blood test: Peripheral blood examination, Biochemical examination,

High-sensitive CRP

****4 weeks after the completion of the administration****

The items below will be tested at the outpatient clinic:

1. Subjective symptom: QOL score (SF-36, SGRQ), MRC dyspnea scale
2. Examination: Blood pressure, Heart rate, Auscultation
3. Body height, Body weight, BMI
4. Blood test: Peripheral blood examination, Biochemical examination,

High-sensitive CRP

1. Arterial blood gas analysis (measured in recombency)
2. Pulmonary function test (flow volume and spirometric evaluation)
3. 6-min Walk Test
4. Grip strength
5. Respiratory Muscle Strength

**8) Safety Assessments: All evaluation will be performed under the blinded condition**

(a) Serious adverse event

When a serious adverse event (including acute exacerbation and infections) occurs, the investigator will promptly reports the name of the adverse event, date of administration initiation, onset date, treatment, and outcome at the time of the description to the study director. The trial will be discontinued when the study director judges as continuation is difficult. The study director will investigate the causal relationship with the allocated drug and follow the patient until his/her recovery as much as possible.

(b) Clinical examination for safety assessments (Blood tests)

Haematology and Biochemistry are to be measured before the administration; Weeks 1, 2 and 3 after start of the administration**;** Week 7 after start of the administration, i.e., 4 weeks after the completion of the administration, as well as at any time if clinically indicated**.**

**9) Side effects (Adverse drug reaction)**

Other than unexpected risks, such as allergy, feelings of enhanced gastrointestinal peristalsis, hunger, heat of the trunk, and mild blood pressure reduction are considered. Feeling unwell and vertigo may occur, although these have not been reported in Japan or other countries.

**10) Discontinuation of clinical trial**

The trial will be immediately discontinued when the following conditions are met:

(a) Notification of withdrawal from the trial by the patient

(b) Judgment by the investigator or subinvestigator

i) Development of an adverse event judged as resulting in discontinuation by the investigator or subinvestigator

ii) Conflict with the inclusion or exclusion criteria

 In case of i), the trial will be immediately discontinued and the adverse event will be treated.

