**2) Subjects of the clinical study**

**Study patients**

A) **Trial Inclusion Criteria;** Patients who meet all conditions below:

a) Severe to very severe COPD (forced expiratory volume in one second

(FEV1)/forced vital capacity (FVC) of less than 70% and FEV1 percent predicted of less than 50%)

b) Underweight (body mass index (BMI) < 21 kg/m2)

c) Clinically stable and able to participate in pulmonary rehabilitation

d) Between 20 and 85 years old

e) Signed the agreement for participation in this study

B) **Trial Exclusion Criteria**; Participants were excluded for any of the following.

a) Malignant tumours

b) Active infection

c) Severe heart disease

d) Hepatic dysfunction (serum aspartate aminotransferase and alanine

aminotransferase levels at least twice the upper limit of normal)

e) Renal dysfunction (serum creatinine levels ≥ 2.0 mg/dl)

f) Asthma

g) Definitely or possibly pregnant

h) Change in drug regimen within 4 weeks before participation in this study

i) Judged to be unable to participate in this study by their physician.

**3) Pulmonary rehabilitation** (on an inpatient basis)

a) Education and instruction of patients and their families

b) Physical therapy: Conditioning (relaxation, flexibility training, instruction in breathing, and synchronization of motion)

c) Exercise training: Method of exercise training: Exercise training was conducted in 3 sets daily, every weekday for 3 weeks (i.e. 15 days) at high-intensitytargets using electromechanically braked cycle ergometers. The initial exercise level of each set was set for 6 min at the work rate corresponding to 60% of the peak Vo2 achieved on the baseline cardiopulmonary exercise testing (CPET). As tolerated by the subject, the exercise duration was initially increased to 10 min. After that, the training work rate was increased by 5 W and then extended to the work rate corresponding to 80% of the baseline peak Vo2. If the subject found the set intolerable, it was reduced to its previous setting. Supplemental oxygen was used if necessary to maintain an oxygen saturation > 90% during exercise training.

(It is assumed that no patient will dropout from this program. Accordingly, the number of dropouts will not differ between the active drug and placebo groups even if exercise tolerance is improved by ghrelin, i.e., all subjects can equally obtain an improvement by exercise therapy, and ghrelin administration is expected to add an improvement.)

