**VI Adverse events**

1. **Actions taken to handle adverse events**

When an adverse event occurs in a patient, and the event is judged as requiring treatment by the investigator or subinvestigator, the best treatment will be provided to the patient. The investigator will promptly report it to the efficacy and safety committee. Since the investigator cannot judge whether the patient belongs to the active drug or placebo group at the time of the occurrence of the adverse event, the efficacy and safety committee will open the key code allocation table distributed before study initiation by the person responsible for test drug allocation to identify whether the patient is treated with the active drug or placebo, and judge the possibility of causal relationship between the adverse event and ghrelin. When the investigator or subinvestigator judges that continuation of the trial is difficult due to the adverse event, the trial will be discontinued, and the patient will be followed until recovery to the original condition. Regarding the laboratory test values, blood pressure, and pulse rate, values judged as abnormal with clinical significance by the investigator or subinvestigator will be handled as adverse events.

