**VII Ethical conduct of the study**

1) The study will be conducted in conformity with the ethical principles of the Helsinki Declaration and the study protocol after examination and approval by the Ethics Committee of each institution.

2) **Merits and demerits of the subjects**

a) Merits

Improvement of exercise tolerance and energy metabolism by ghrelin may be expected in the active drug group. Pulmonary rehabilitation performed in both active drug and placebo groups may improve dyspnea and exercise tolerance.

b) Demerits

Improvement of exercise tolerance and energy metabolism by the drug cannot be expected in the placebo group. Since the above merit expected in the active drug treatment group has not been established, the patients will be involved as collaborators for the study.

3) **Consent**

a) Preparation of explanatory document

(1) Investigators will prepare explanatory document to obtain consent from subjects to

participate in the study. The document will be revised as needed. The explanatory document must contain the items presented in b).

(2) The prepared or revised explanatory document is to be approved by the Ethics Committee

of each institution before the use.

b) Descriptions in the explanatory document

The explanatory document is to contain the following items:

(1) The objective of the clinical study is research.

(2) Objective of the clinical study

(3) Study method (inclusion criteria of subjects)

(4) Planned period of subject participation in the study

(5) Planned number of subjects participating in the study

(6) Expected risks and inconveniences (When no merit is expected for subjects, it must be informed to the subjects.)

(7) The presence or absence of other treatment methods and expected important merits and risks of these when patients are selected for the subjects

(8) Compensation and treatment that subjects can receive when health damage related to the clinical trial occurs.

(9) Subjects participate in the clinical trial by their own will and can reject or withdraw the participation any time. They will not be handled disadvantageously or lose benefit that they should receive due to rejection or withdrawal of the participation.

(10) When information which may influence subjects’ will to continue participation is obtained, it will be promptly informed to subjects.

(11) Conditions and reasons to discontinue participation in the study

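### The stopping rule does not separate stopping study drug from leaving the trial, so a patient stopped during dosing could miss the primary outcome visits

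*Protocol*

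**What the plan says.** Section V.10 opens with "The trial will be immediately discontinued when the following conditions are met" and lists the triggers: (a) the patient withdraws; (b-i) an adverse event that the investigator or subinvestigator judges to require stopping; (b-ii) "ii) Conflict with the inclusion or exclusion criteria". For (b-i) it adds: "In case of i), the trial will be immediately discontinued and the adverse event will be treated". This is a rule for the individual patient, since stopping the whole study has its own section (VIII).

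What follows a stop is described only as safety care. For serious adverse events, section V.8 has the study director "follow the patient until his/her recovery as much as possible". Section VI.1 says that "the trial will be discontinued, and the patient will be followed until recovery to the original condition". Neither mentions SGRQ or the walk test. For (b-ii) no later contact is described.

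The two primary outcomes, SGRQ and 6-minute walk distance, are measured before administration, at Week 3 and at Week 7 from the start of administration (V.7; these appear as Weeks 1, 4 and 8 in the V.11 schedule). Section V.4 places evaluation of the effect after dosing is complete. Section V.7 equates Week 7 with four weeks after dosing ends.

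**The concern.** Ending assessment is legitimate when a patient withdraws from the trial. It is not a necessary consequence of an adverse event or an eligibility problem: study drug can stop while the patient stays under observation. The rule treats the three cases alike, so a site that follows it literally has no instruction to carry out the remaining SGRQ and walk tests.

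The patients lost this way would not be a random subset. Section V.8 counts exacerbations and infections as serious events ("When a serious adverse event (including acute exacerbation and infections) occurs"), so those stopped would tend to be the sicker ones, and the chance of a stop may depend on treatment. A comparison limited to patients with data would then no longer be the comparison that randomisation set up. This cannot be left to a statistical analysis plan, which can choose how to handle missing values but cannot recover visits that were never held.

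**Working it through.** **1. Text check: does any section keep a stopped patient in the outcome visits?**

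- V.10 (stopping rule): ends the trial for the patient and treats the adverse event. No outcome visit is mentioned.
- V.8 and VI.1 (adverse events): follow-up to recovery. No outcome visit is mentioned.
- V.7 and V.11 (assessments and schedule): Week 3 and Week 7 visits are listed without restriction to patients on drug, but also without any statement that stopped patients attend.
- V.4 and V.7 (timing): both presuppose completed dosing. For a patient stopped at the end of Week 1, four weeks after the last dose is Week 1 + 4 = Week 5, whereas the visit counted from the start of administration is Week 7. The text gives no single date for this patient.

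No section says that assessments cease, and none says that they continue. A patient stopped during dosing could lose both post-baseline measurements. One who has already had the Week 3 examination could lose only Week 7.

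**2. Effect of each loss on a completer comparison**

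Input: 30 per arm (Summary, item 9). Let R be the mean outcome of the patients who remain, S the mean that the k stopped patients would have shown, and gap = R − S.

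All-randomised mean = [(30 − k)R + kS]/30 = R − (k/30) × gap

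The completer mean therefore differs from the all-randomised mean by (k/30) × gap. With a common gap in both arms, the shift in the treatment difference is (k1 − k2)/30 × gap:

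- 1 net extra loss: 1/30 = 3.3% of the gap
- 2: 2/30 = 6.7%
- 3: 3/30 = 10%

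The document does not give the gap. If it is assumed to be 0.5 to 1.0 SD, one net extra loss shifts the difference by 0.017 to 0.033 SD, and three by 0.05 to 0.10 SD.

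For scale, section IX.3 plans a 90% confidence interval for the difference in means. Its half-width with 30 per arm is t(0.95, 58) × sqrt(1/30 + 1/30) = 0.432 SD. At a gap of 1 SD, one net extra loss is 0.033/0.432 = about 8% of that half-width, and three are 0.10/0.432 = about 23%.

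**3. How many stops might occur?**

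The Protocol gives no stop rate, so the rates p below are assumptions for (b)-type stops. Expected number = 60p; chance of at least one = 1 − (1 − p)^60.

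| p | Expected stops | Chance of at least one |
| --- | --- | --- |
| 1% | 0.6 | 45% |
| 2% | 1.2 | 70% |
| 5% | 3.0 | 95% |
| 10% | 6.0 | 99.8% |

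In the background section on previous clinical studies, all 7 COPD and all 10 heart-failure pilot patients completed. The one-sided 95% upper limit for 0 of n is 1 − 0.05^(1/n), which gives 34.8% for n = 7 and 16.2% for n = 17. The second figure pools two diseases. The pilots do not exclude a relevant stop rate, nor do they suggest one. In a three-week inpatient course the low end of the table is plausible.

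**The case against.** The strongest reply is that the harm is inferred from silence. The Protocol uses the word trial loosely, for one patient in V.10 and for the whole study in VIII, and in V.10 it may simply mean the trial treatment. The visit schedule is not restricted to patients on drug. This stands as far as it goes: a reader might infer that the Protocol orders assessments to end, and it does not say so. But if treatment was meant, the wording still needs correcting, because sites can read it either way.

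Three further inferences are tempting and should not be drawn.

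- The consent list in VII.3, item (11), "Conditions and reasons to discontinue participation in the study", might look like confirmation that stopping means leaving. It is only a topic that the explanatory document must cover and sets no rule.
- Since "Clinically stable and able to participate in pulmonary rehabilitation" and absence of active infection are entry conditions, (b-ii) might seem to remove patients who deteriorate on treatment. Nothing says that entry criteria continue to apply after dosing starts. Eligibility is confirmed before allocation (V.1), and an exacerbation on treatment would already fall under (b-i).
- The no-dropout assumption in V.3 might be taken to rest on the pilots, or to settle the matter. It cites no basis and concerns the rehabilitation program, not this rule.

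It is also fair to say that the fix recovers only part of what could be lost. A patient too ill to walk will still have no 6-minute walk distance. The SGRQ, and the reason for the missing walk, can still be obtained in many such cases.

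**Conclusion.** The point holds as a defect in a stated rule. Section V.10 attaches one consequence to three different situations, and no other section limits it. Followed literally, it could lose primary outcomes selectively after randomisation, when the visits needed to avoid this are already scheduled.

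It does not support a claim that outcomes will be lost or that the result will be materially biased. The number of stops is probably small, about 0.6 to 1.2 among 60 patients at assumed rates of 1% to 2%. A sizeable shift would need several net extra stops in one arm together with a large gap, and the document predicts neither. The illustrations rest on assumed stop rates, an assumed gap of 0.5 to 1.0 SD, and an analysis restricted to patients with data. This is a cheap improvement worth making, not a flaw that undermines the design.

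**What to change.** Amend section V.10 as follows.

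1. State that (b-i) stops study drug only. The existing Week 3 and Week 7 assessments, dated from the start of administration, continue where medically fit unless the patient withdraws consent to follow-up. If the walk test is unsafe, still collect the SGRQ and record why the walk was not done.
2. For (b-ii), state that a patient found ineligible after randomisation may stop study drug but stays under the scheduled observation.
3. Leave (a) as it is.

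The cost is small. No visit is added to the schedule, but a patient stopped and discharged early would occasionally have to return for Week 3. Some measurements would be taken off treatment and may slightly dilute the estimated effect.

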**11) Schedule of the clinical trial from admission to discharge**

The duration of hospital stay will be about one month. Re-examination will be performed one month after discharge.

Week 0: Submission of written consent

Week 1: Examination before administration

Weeks 2-4: Ghrelin or placebo administration

End of Week 4: Examination after administration

Week 5: Discharge

Week 8: Examination at one month after the completion of the administration

**Schedule of the clinical trial**

| Date | / | / | / | / | / | / | / | / | / |
| --- | --- | --- | --- | --- | --- | --- | --- | --- | --- |
| Week | 0 | 1 | 2 | 3 | 4 | 5 | 6 | 7 | 8 |
| Informed consent production | ○ |  |  |  |  |  |  |  |  |
| Ghrelin administration |  |  |  |  |  |  |  |  |  |
| Subjective symptom |  | ○ |  |  | ○ |  |  |  | ○ |
| Examination: BP, HR |  | ○ | ○ | ○ | ○ |  |  |  | ○ |
| Body weight, Height , BMI |  | ○ | ○ | ○ | ○ |  |  |  | ○ |
| Blood drawing (20mL and serial measurement) |  | ○ |  |  | ○ |  |  |  |  |
| Arterial blood gas analysis |  | ○ |  |  | ○ |  |  |  | ○ |
| Pulmonary function test |  | ○ |  |  | ○ |  |  |  | ○ |
| Food intake |  | ○ |  |  | ○ |  |  |  |  |
| 6-min Walk Test |  | ○ |  |  | ○ |  |  |  | ○ |
| DEXA |  | ○ |  |  | ○ |  |  |  |  |
| Holter ECG |  | ○ |  |  | ○ |  |  |  |  |
| CPET |  | ○ |  |  | ○ |  |  |  |  |
| Grip strength |  | ○ |  |  | ○ |  |  |  | ○ |
| Respiratory Muscle Strength |  | ○ |  |  | ○ |  |  |  | ○ |
| Blood drawing 10mL |  |  | ○ | ○ |  |  |  |  | ○ |

**12) Blinding**

The person responsible for test drug allocation will confirm and record non-identifiability of the appearances and packages of the active drug and placebo before allocation. The persons responsible for allocation and in charge of allocation will not disclose the allocation information they acquire through the work until key open. Labeling on the outer boxes containing the test drugs will follow the law, and the study name, number of vials, ‘for study use’, expiry date, and storage conditions will be described. The person responsible for test drug allocation will establish an allocated drug management procedure and record in and out.

